## Methods: participants, interventions, and outcomes

### Study setting {9}

Patients who are scheduled to undergo laparoscopic radical resection for colorectal cancer will be recruited from the Colorectal Surgical In-patient Department of Cancer Hospital Chinese Academy of Medical Sciences (CICAMS). Patients are considered for inclusion if they meet the criteria as defined below.

### Eligibility criteria {10}

#### Inclusion criteria

To enroll in the study, subjects must (1) be diagnosed with colorectal cancer based on cytological or histopathological features, (2) be scheduled to undergo laparoscopic radical resection for colorectal cancer, (3) age between 18 and 80 years old, (4) consent to participation and completion of the full treatment process and be able to sign the informed consent form, and (5) postoperative blood examination showed no obvious abnormality.

#### Exclusion criteria

Patients may not participate in the study if they are as follows: (1) patients converted to open surgery; (2) have emergency such as acute intestinal obstruction or intestinal perforation; (3) have a history of other malignant neoplasms or are having other malignant tumors concurrently; (4) have undergone vagotomy or colostomy; (5) have preexisting conditions such as severe cardiovascular disease, hepatic, renal, hematopoietic, immune system conditions, and psychiatric disorders; (6) have skin allergies or infections; (7) are anxious or fearful of acupuncture treatments; (8) have been prescribed adrenergic agonist or antagonist, cholinergic, or anticholinergic medications that affect gastrointestinal function for the past 1 month; (9) have severe postoperative complications that require admission to the intensive care unit; (10) are pregnant or lactating; and (11) have American Society of Anesthesiologists (ASA) physical status classification IV.

### Who will take informed consent? {26a}

Based on the above criteria, to confirm whether a patient undergoing colorectal cancer surgery is eligible to participate in this study after screening, the patient has been assessed as qualified by the treatment group, and the surgeon will fill in the preliminary study information of the patient. Patients were invited to meet with researchers and doctors to discuss any remaining issues and sign informed consent.

### Additional consent provisions for collection and use of participant data and biological specimens {26b}

In this study, biological samples of participants will be collected as acupuncture safety indicators, which will be used as additional terms when participants sign the informed consent form, inform patients of the purpose of biological samples and possible privacy risks, and obtain the consent of participants.

## Interventions

### Explanation for the choice of comparators {6b}

The control group received routine postoperative ERAS protocol. The control group can take medicine according to the doctor’s advice.

### Intervention description {11a}

Study subjects from both groups will receive standardized perioperative care from ERAS protocols (detailed nursing and care plans will be facilitated by the CICAMS and would not be intervened by investigators) (Table 1).

**Table 1 Tab1:**
[figure not shown]
Time schedule of enrollment, interventions, and assessments

#### Perioperative care guided by ERAS protocols

1. Preoperative education, unconventional preoperative mechanical bowel preparation

2. Standardize anesthesia scheme, intraoperative warming

3. Comprehensive postoperative analgesia, remove the urinary catheter as soon as possible, early postoperative oral feeding, and early postoperative ambulation

### Acupuncture group

Patients in AG will receive acupuncture treatment in addition to perioperative care guided by ERAS protocols. Acupuncture treatment will be performed once daily, consecutively over 4 days, starting on the first day after the laparoscopy. Patients will assume a supine position for the treatment. Treatment will be carried out by a licensed acupuncturist who holds a China Acupuncturist Certification, with at least 2 years of clinical experience in acupuncture. The site of insertions will be swabbed and disinfected with 75% alcohol prior to needle insertion. Sterile, single-use acupuncture needles with diameter 0.30 mm and length 40 mm (China Suzhou, Huatuo) are used. Acupuncture points are selected based on Traditional Chinese Medicine (TCM) theory and clinical experience: ST36 Zusanli, ST37 Shangjuxu, PC6 Neiguan, LI4 Hegu (Fig. 2). Exact locations and depth of insertions are referenced from the 2006 National Standards of the People’s Republic of China (GB/T12346-2006) “Nomenclature and Location of Acupuncture Points” [16] (Table 2). After insertion of needles, stimulation of acupoints will be performed every 10 min, and each operation lasts at least 10 s, through lifting-thrusting and twirling-twisting manipulations, to achieve sensations of *deqi*. Needles are kept inserted for 30min.

**Fig. 2 Fig2:**
[figure not shown]
The location of ST36, ST37, L14, and PC6. ST36 is the Zusanli acupoint; ST37 is the Shangjvxu acupoint; L14 is the Hegu acupoint; PC6 is the Neiguan acupoint

**Table 2 Tab2:** Locations and manipulations of the acupuncture group and control group

Group	Acupoints	Locations	Needle insertion	Needle manipulation
Acupuncture group	Neiguan (PC-6)	On the palmar side of the forearm, 2 inches above the transverse line of the wrist, between the palmaris longus tendon and the flexor carpi radialis tendon	Perpendicular needle insertion at depth of 10–30 mm	Manipulation and De-qi sensation felt by practitioner and patient
	Hegu (LI-4)	On the back of the hand, between the first and second metacarpal bones, at the midpoint of the radial side of the second metacarpal bone	Straight needle insertion at depth of 10–30 mm	
	Zusanli (ST-36)	On the anterolateral side of the calf, 3 inches below the nose, a transverse finger (middle finger) from the front edge of the tibia	Straight needle insertion at depth of 30–60 mm	
	Shangjixu (ST-37)	On the anterolateral side of the calf, 6 inches below the nose, a transverse finger (middle finger) from the front edge of the tibia	Straight needle insertion at depth of 30–60 mm	
Control group	Non-intervention			

### Control group

Patients in CG will only receive ERAS care with no acupuncture intervention.

### Criteria for discontinuing or modifying allocated interventions {11b}

Patients can leave the study at any time for any reason if they wish to do so without any consequences. The patient’s participation in this study can also be ended by the investigator if the patient is uncooperative and/or does not attend study visits. The patient data that have been collected up to that moment will be included in the analysis. In case too many data are missing, the patient will be replaced by a new patient. If there are adverse events or postoperative complications, the study will be terminated early. In case of illness, patients will be asked to contact the primary investigator. Patients that are discovered after surgery not to meet the criteria will not receive acupuncture treatment and will be treated according to the standard of care. These patients will be removed from the study. Patient data included up to that moment will be included in the analysis.

Criteria for study termination include the following: ① The pain of acupuncture was intolerable or serious adverse reactions occurred; ② during the treatment, the symptoms worsened or other critical diseases appeared, and the patients could not continue the treatment; ③ researchers found that there were serious safety problems; ④ because of various reasons cannot adhere to the treatment.

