#### Implementation {16c}

After ensuring patients fulfill inclusion criteria and informed consent forms are obtained from them, the envelopes are opened by the acupuncturist and acupuncture treatment is carried out (the acupuncturist is excluded from assessment and statistical analytic process as blinding of the acupuncturist cannot be achieved). The study group will be revealed at the same time to both the patient and researcher.

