### Assignment of interventions: blinding

#### Who will be blinded {17a}

Throughout the study, the statisticians and evaluators are blinded, so that independent assessments and statistical analysis can be carried out. The subjects in the control group could not be blinded due to their particularity. Acupuncturists were not blinded in this study.

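### Rules that end participation, not just acupuncture, can leave randomised patients without a first-flatus time, and replacing those patients does not restore the intention-to-treat comparison

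*Protocol article*

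**What the plan says.** All of the following is in the protocol article.

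- **Ending participation (section 11b).** Patients may leave at will. In addition, a patient's "participation in this study can also be ended by the investigator if the patient is uncooperative and/or does not attend study visits". For patients who stop in these ways, "The patient data that have been collected up to that moment will be included in the analysis".
- **Replacement (section 11b).** The next sentence reads: "In case too many data are missing, the patient will be replaced by a new patient". It gives no threshold for too many.
- **Termination list (section 11b).** The same section has a list introduced as criteria for study termination. One item is "The pain of acupuncture was intolerable or serious adverse reactions occurred"; another covers patients who "because of various reasons cannot adhere to the treatment". A separate sentence says that adverse events or complications bring the study to an early end.
- **Who knows the allocation.** Section 16c: "The study group will be revealed at the same time to both the patient and researcher". Section 17a: "the statisticians and evaluators are blinded".
- **Control arm.** "Patients in CG will only receive ERAS care with no acupuncture intervention".
- **Primary outcome and analysis.** The outcome is one time per patient, from return to the ward until first flatus. Section 20a compares quantitative outcomes by t test or Wilcoxon rank-sum test. Section 20c promises an intention-to-treat analysis of the primary outcome.
- **Retention (section 18b).** Patients may stop acupuncture at any time and, if possible, are still asked to complete the 1-month survey.

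**The concern.** Intention-to-treat compares everyone randomised, in the arm to which they were randomised. That requires the outcome to be collected whether or not treatment continues. Taken at its word, section 11b can end a patient's participation for reasons tied to the acupuncture itself, at a time when patient and researcher know the arm. If this happens before first flatus, there is no value to analyse. The patient brought in as a replacement is a different person and does not stand in for the missing outcome.

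One exit route, intolerable needling pain, cannot occur among controls. Failure to keep to treatment will arise mainly in the acupuncture arm. Worsening symptoms and complications can arise in either arm, but are plausibly related to slow bowel recovery. If acupuncture patients who would have recovered late are lost more often than comparable controls, the acupuncture mean is pulled down and the trial favours acupuncture for a reason other than its effect.

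**Working it through.** **1. Which patients are exposed.** A patient who leaves after first flatus already has the primary value, and section 11b keeps data collected up to exit. Only exits before first flatus matter for the primary outcome. The document does not say how many to expect.

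**2. The plan's own sample-size figures (section 14).** Inputs: difference 8 h, SDs 12.28 and 14.57, α = 0.05, power 0.90, one-sided; stated result 68 per arm, raised to 160 in total for 20% dropout.
- Root-mean-square SD = √((12.28² + 14.57²)/2) = 13.47.
- The normal formula gives 49 per arm one-sided and 60 two-sided (50 and 61 with the t distribution), so 68 is not reproduced.
- 136/0.80 = 170, whereas 136/0.85 = 160, so 160 keeps 136 only up to 15% loss.

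These mismatches are a separate matter. What counts here is the margin. Two-sided Welch power for 8 h is 96.2% at 80 per arm, 93.0% at 68, 91.5% at 64 and 90.2% at 61. A 20% loss from 160 leaves 128, or 64 per arm.

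**3. Illustration of the bias.** Assumptions, none taken from the document: no true effect; 80 per arm; a fraction p of patients in both arms reaches first flatus 12 h later than the rest; SDs as in section 14; those patients are lost before flatus in the acupuncture arm only.
- Bias = p × 12 h. For p = 5% this is 0.6 h; for p = 10% it is 1.2 h. Against the 8 h target these are 0.6/8 = 7.5% and 1.2/8 = 15%.
- Two-sided rejection rate ≈ Φ(−1.96 + b/SE) + Φ(−1.96 − b/SE). For p = 10%, 72 against 80 patients: SE = √(12.28²/72 + 14.57²/80) = 2.18 h and b/SE = 0.55, giving 0.079 + 0.006 = 8.5%.

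Simulation with the Welch test (20,000 runs without refilling; 40,000 with the arm refilled):

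| Loss before flatus | Acupuncture arm refilled to 80? | Bias | False-positive rate |
|---|---|---|---|
| 5%, acupuncture only | no | 0.60 h | 5.8% |
| 5%, acupuncture only | yes | 0.60 h | 5.8% |
| 10%, acupuncture only | no | 1.2 h | 8.5% |
| 10%, acupuncture only | yes | 1.2 h | 8.6% |
| 10% acupuncture, 5% control | no | 0.64 h | 5.8% |
| 10% in both arms | no | 0 h | 4.9% |

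The Wilcoxon test gives 5.6% and 7.9% in the two acupuncture-only cases without refilling (12,000 runs). Doubling the error rate to 10% would need about 1.43 h of bias, for example 10% excess loss with a 14.3 h delay.

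**4. A different loss model.** Let the chance of exit rise with slowness of recovery, in the acupuncture arm only, with every exit replaced and SD 14.57 in both arms (4,000 runs). At 5%, 10% and 20% exits, the spurious difference is about 0.4, 1.0 and 2.0 h, and the error rate about 5%, 8% and 15%. When exit is unrelated to recovery, the error rate stays near 5%.

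**5. What the comparison shows.** With and without refilling, the results are practically the same. The bias comes from not observing the outcome; replacement neither causes nor repairs it.

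**The case against.** - **The replacement sentence is not the source of harm.** This stands. A reader might infer from section 11b that replacement itself biases the trial. The table shows otherwise, and deleting that sentence alone would leave any bias in place.
- **There is no outright contradiction with intention-to-treat.** This stands in part. A reader might infer that replaced patients are dropped from the analysis, but nothing says so. The sentence just before replacement keeps their data, and replacing can be read as recruiting one more patient. Kept data still cannot supply a flatus time that was never recorded.
- **The list may mean stopping treatment only.** Its section heading concerns discontinuing allocated interventions, and section 18b separates stopping acupuncture from leaving. That reading is reasonable and probably intended. The list nevertheless speaks of terminating the study, so staff following it literally could stop recording flatus.
- **Missing-data handling and the blinding of whoever decides on replacement belong in a fuller document.** Accepted. Neither omission is counted here; the point rests on rules the article does state.
- **Few patients may be affected, and the direction is assumed.** Both stand. First flatus may come early, and missing data could as easily concern the 1-month outcomes. Unblinded controls might also leave, which could reverse the bias.

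**Conclusion.** The point holds as a defect in rules the protocol states. Applied literally, section 11b can end outcome collection before first flatus, by routes partly specific to the acupuncture arm and after allocation is known. That sits badly with the intention-to-treat primary analysis, and replacement does not put it right.

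A reader might go further and infer that the trial will be biased towards acupuncture. The document does not support that: it gives no loss rate by arm and no information on recovery in those lost. The 0.6 to 1.2 h and 6% to 8.5% figures rest wholly on the assumed 5% to 10% one-sided loss and 12 h delay. With loss balanced in rate and kind, or unrelated to recovery, there is no bias. The exposure is possible and probably modest, and it is cheap to remove.

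**What to change.** **Main change (section 11b).**
- Retitle the list *Criteria for stopping acupuncture*, in line with its section heading and section 18b.
- Reword the sentence on adverse events and complications so that they may stop acupuncture but not follow-up. Complications are themselves recorded as outcomes and adverse events of special interest.
- State that first flatus and the 1-month outcomes are recorded for every randomised patient unless consent is withdrawn, and that each patient is analysed in the allocated arm.

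**Secondary change.** Delete the replacement sentence, or state that any replaced patient stays in the intention-to-treat set. Rely on the dropout allowance in section 14.

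**Cost.** A wording amendment notified to the ethics committee, and continued collection of outcomes the trial already gathers from the ward, the medical record and the 1-month contact. No extra patients are needed. Without replacement, a 20% loss leaves 64 per arm rather than the stated 68, and two-sided power for 8 h is 91.5% instead of 93.0%, still above the planned 90%.

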### Provisions for post-trial care {30}

After waiting for the end of the experiment, the control group will receive 4 acupuncture treatments free of charge. If the subject is injured by acupuncture during the study period, acupuncture should be stopped immediately, symptomatic treatment should be given free of charge, and psychological counseling should be given to the patient at the same time. If the injury is serious, invite relevant experts for treatment and compensate for medical expenses.

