#### Composition of the data monitoring committee, its role, and reporting structure {21a}

No data security monitoring board (DSMB) was designated in this study. The decision was based on the absence of serious adverse events in the pre-trial. In addition, since this is not a double-blind trial, there is no need for DMSB to protect researchers and doctors from blindness. A colorectal cancer surgeon will be designated as the safety officer for this study. In case of serious adverse events, the safety officer will be contacted within 48 h. The safety officer will assess whether the serious adverse event is (definitely or possibly) related to the treatment. If there is a (possible) handling relationship, further safety measures will be taken based on the advice of the safety officer.

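### Section {11b} ends the study on any adverse event or complication, which contradicts its own termination list and the plan to record complications as outcomes; the level at which each criterion acts must be stated

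*Protocol article*

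**What the plan says.** All references are to the protocol article.

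- **Section {11b}, first paragraph:** "If there are adverse events or postoperative complications, the study will be terminated early". The sentence does not qualify the event by grade, cause or count, and it names no decision-maker.
- **Section {11b}, list headed as criteria for study termination:** item 1 is "The pain of acupuncture was intolerable or serious adverse reactions occurred"; item 2 is "the symptoms worsened or other critical diseases appeared, and the patients could not continue the treatment"; item 3 is "researchers found that there were serious safety problems"; item 4 is inability, for whatever reason, to keep to the treatment.
- **Section {12}, secondary outcomes:** postoperative complications (fever, pneumonia, wound infection and bleeding are among the examples) are a secondary outcome, graded by Clavien Dindo. Adverse events are defined to include both these complications and acupuncture events such as subcutaneous hematoma. Readmission and QLQ-C30 are assessed 1 month after the operation.
- **Section {22}:** all adverse events are recorded, and fever, bleeding, wound infection, anastomotic leakage and others are events of special interest.
- **Section {21a}:** "In case of serious adverse events, the safety officer will be contacted within 48 h". The officer judges relatedness and, if a relation is at least possible, "further safety measures will be taken based on the advice of the safety officer".
- **Section {30}:** "If the subject is injured by acupuncture during the study period, acupuncture should be stopped immediately".
- **Sections {21a}, {5d} and {21b}:** there is no data monitoring board, no steering committee and no interim analysis.

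**The concern.** The unqualified sentence and the list under it give different thresholds for what appears to be the same action. The sentence also makes the occurrence of a planned outcome a reason to end the study in which that outcome is to be counted.

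Site staff cannot tell from the text whether a fever on day 2 ends the trial, ends that patient's participation, stops that patient's acupuncture, or is simply recorded. With no monitoring board, steering committee or interim analysis, these sentences carry most of what the article says about stopping.

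What is at stake depends on how the sentence is applied. One application makes the trial inoperable. The other removes follow-up selectively from the patients who do worst.

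**Working it through.** **Step 1. Compare the texts in {11b}.**

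| Place | Trigger | Level at which it makes sense |
|---|---|---|
| Unqualified sentence | any adverse event or complication | written as the study |
| List item 1 | intolerable needle pain or a serious reaction | mainly one patient |
| List item 2 | worsening or critical illness, unable to continue | one patient |
| List item 3 | serious safety problems found by researchers | the trial |
| List item 4 | cannot adhere | one patient |

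If any adverse event already terminates, the word serious in items 1 and 3 has no function. If seriousness is required, the unqualified sentence is wrong. This conflict exists whichever level is meant.

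**Step 2. Compare with {12} and {22}.** Complications are to be graded in all patients and reported. A rule that ends observation at the first complication is incompatible with that plan, whether observation ends for everyone or for that patient.

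**Step 3. Size of the trial-level reading.** Inputs: 160 planned patients (section {14}) and a per-patient probability *p* of at least one adverse event or complication. The article gives no *p*, so a range is assumed, with patients treated as independent. The background calls postoperative gastrointestinal dysfunction a common complication, but attaches no rate.

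P(at least one patient in 160) = 1 − (1 − p)^160; P(136 patients without an event) = (1 − p)^136; mean number of patients up to the first event = 1/p. The figure 136 is the number needed before dropout in {14}.

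| Assumed p | P(at least one in 160) | P(136 with none) | Mean patients to first event |
|---|---|---|---|
| 1% | 1 − 0.99^160 = 0.80 | 0.25 | 100 |
| 2% | 1 − 0.98^160 = 0.96 | 0.064 | 50 |
| 5% | 1 − 0.95^160 = 0.9997 | 0.0009 | 20 |

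The trial-level rule would also act before the safety officer's assessment of relatedness in {21a} could matter, because any event, serious or not, would already have ended the trial.

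**Step 4. Consequence of the patient-level reading.** Section {11b} says that data gathered until a patient leaves are analysed. If participation ends at the first complication, then for that patient:

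- later complications are not counted;
- 1-month readmission is not observed;
- 1-month QLQ-C30 is not obtained.

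The loss depends on the outcome itself: those removed are by definition those with complications. It is also unequal between arms by construction, because acupuncture events count as adverse events under {12} and can occur in only one arm. The size of the bias cannot be computed without event rates by arm, which the article does not give.

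**The case against.** The strongest reply is that the sentence was never meant for the trial. Section {11b} concerns discontinuing or modifying allocated interventions. Most sentences around it are about one patient leaving, being replaced or being removed, and items 2 and 4 of the list can describe only a patient. The plan to count complications also argues against a rule that ends the trial at the first one. This stands: the context favours a patient-level reading, and the probabilities in step 3 say nothing under it. It does not clear the sentence. The same paragraph speaks of a patient's participation when one patient is meant, so the literal text remains trial-level. The patient-level reading keeps the conflict with the seriousness requirement in the list and brings the loss of follow-up in step 4. Section {18b} does ask, where possible, for the 1-month survey from patients who choose to stop acupuncture, but it does not say that patients ended under {11b} stay in follow-up.

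A reader might go further and infer that {11b}, {21a} and {30} are competing stopping rules that cannot be applied together. The text does not support that. Section {21a} is a notification and advice duty that does not mention termination, and {30} stops acupuncture for one injured patient. Both can operate beside {11b}.

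A reader might also set the 48 h limit against "Acupuncture treatment will be performed once daily, consecutively over 4 days" and conclude that the safety review comes too late for the patient concerned. That does not follow either. The 48 h is a ceiling for contacting the officer and does not govern whether the next session takes place. Items 1 and 2 of the list and section {30} allow acupuncture to stop sooner, and {22} has acupuncture events recorded at once.

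**Conclusion.** The point holds as an internal contradiction in a stated rule; it is not a complaint about missing detail. The unqualified sentence in {11b} disagrees with the list below it and with the handling of complications in {12} and {22}, and it fails on either reading.

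At trial level, early termination is likely at an assumed 1% event rate (0.80) and close to certain from about 2% (0.96; 0.9997 at 5%). These figures rest on the assumed rates and on independence between patients. At patient level, which the context makes the more probable intention, the harm is selective loss of later complications, readmission and quality of life; its direction and size cannot be quantified from the article.

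The matter should be corrected, but it does not show that the trial's safety provisions are mutually incompatible or that the safety officer's review is too slow.

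**What to change.** Reconcile sections {11b}, {30}, {12}, {21a} and {22} so that one set of criteria applies throughout:

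- For each criterion, state whether it stops acupuncture only, ends one patient's participation or stops the trial.
- For each, name who decides, and say how the decision relates to the safety officer's assessment in {21a}.
- State that patients whose acupuncture is stopped remain in follow-up for the planned outcomes, including complications, 1-month readmission and 1-month QLQ-C30, unless they withdraw consent.

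Which events lead to which action is a clinical decision for the sponsor, and none is proposed here.

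The cost is a protocol amendment and notification under {25}. No visit, measurement or patient is added, because the 1-month assessments are already planned; the only extra effort is completing them in patients who might otherwise have been taken off study.
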